## Methods

### Overview

We are conducting a feasibility randomized controlled trial (RCT) to evaluate the use of a custom-developed cognitive training program to improve the cognitive function of children aged between 4 and 6 years who were exposed to alcohol in the prenatal stage compared with a control group.

We hypothesize the following:

Post intervention, the intervention group will score higher on psychometric assessments of EFs than the control group.At baseline, alcohol-exposed children (both intervention and control groups) will score significantly lower on psychometric assessments of EFs compared with nonalcohol-exposed children (normative group).Post intervention, the intervention group will score higher on psychometric assessments of EFs than the control group, but lower than the normative group.Post intervention, the intervention group will show greater improvement on psychometric assessments of EFs than the control and normative groups.Improvement in game performance will be correlated with improvement on psychometric assessments of EFs.Improvement in psychometric assessments of EFs will be positively correlated with total time spent playing the game.

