### Measures

The primary outcome is EF, as measured using the NEPSY-II psychometric assessment score. The secondary outcomes are (1) game performance, as measured in the game log files, (2) reaction time, and (3) increase in the level of difficulty of the task.

Additional demographic data will be gathered during the recruitment process. In addition to alcohol use, data will be gathered on age, gravidity, parity, years of schooling, and household income.

All participants will be evaluated using a selection of subtests of the NEPSY-II that measure executive functioning and working memory. Cognitive function, focusing on EFs, will be measured using the NEPSY-II [36]. The NEPSY-II is a compendium of tests based on the Luria theoretical approach to neurological assessment. It is individually administered and has been shown to be successful in diagnosing a range of childhood disorders. The subtests of this test can also be selected based on the specific domains to be tested [37].

Scores obtained on the subtests of the NEPSY-II are compared with the scores of a normative group based on age. The normative group of the NEPSY-II was selected to closely match the US population between 3 and 16 years of age [38]. This group will differ significantly from the populations of interest in this study; however, the NEPSY-II is relatively insensitive to language and culture differences. Although the results need to be interpreted cautiously, the test remains clinically useful [39]. Insensitivity to language is an important feature as the study sample will be drawn from a predominantly Afrikaans-speaking community, which could affect test performance [40].

In the standardization of the NEPSY-II, subtests showed adequate-to-high internal validity. There was no significant practice effect with re-administration of the test in a short space of time (around 3 weeks), supporting its use for both the pre- and postintervention assessments in this study [41]. Inter-rater agreement was high on both the objectively and more subjectively scored test, and the reliability of subtests remained stable [38]. The inclusion of the third group of children not exposed to alcohol in pregnancy will help guide the interpretation of results.

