### Data Analysis

For the primary hypothesis, the postintervention scaled scores of the intervention group will be compared with those of the control group. This will be done using a MANOVA with group membership as the predictor variable and the scaled scores of the 5 NEPSY-II domains (see Table 1) as outcome variables. Discriminant analysis will be done on the outcome of the MANOVA with the domain scores as predictor variables and group membership as outcome variables.

During further analysis, the baseline NEPSY-II scaled scores of the intervention and control groups will be pooled and compared with the scores of the normative group. This will also be done using a MANOVA with group membership as the predictor variable and the scaled scores of the 5 NEPSY-II domains (see Table 1) as outcome variables. Discriminant analysis will again be done on the outcome of the MANOVA with the domain scores as outcome and group membership as predictor variables.

Postintervention NEPSY-II scaled scores (see Table 1) of the intervention, control, and normative groups will be compared using a MANOVA. Group membership will be the predictor variable, and domain scores will be the outcome variables. Discriminant analysis will be conducted with the domain scores as outcome variables and group membership as predictor variables.

Difference scores between baseline and postintervention assessments will be calculated for all participants. These scores will be compared using a MANOVA with group membership as the predictor variable and changes in domain scores (see Table 1) as outcome variables. Discriminant analysis will be done on the results with changes in domain scores as outcome and group membership as predictor variables.

For the secondary hypothesis, the improvement in game performance will be quantified as how many difficulty levels a participant has successfully completed in each of the 3 different stages of the game. This will then be correlated with performance in the NEPSY-II domain scores in a covariance matrix using the Pearson correlation coefficient. A separate analysis will be done including only 6-year-old children using the additional domains tested (see Table 1).

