Additional exploratory analyses will be done comparing the demographic information of the 3 groups. These data will be drawn from the maternal interview. Demographic data on the mothers of the alcohol-exposed children (both intervention and control groups) will be pooled and compared with nonalcohol-exposed children to ascertain if there were significant differences between the 2 groups. This will be done using 2 tailed *t* tests for independent samples. To account for family-wise errors, Bonferroni-adjusted values will also be calculated. The variables to be analyzed are age, gravidity, parity, years of schooling, and income. Tobacco and drug use will also be compared among the alcohol-exposed and nonalcohol-exposed groups using a chi-square test.

Further exploratory analysis will be done on the game logs. Reaction time in the various stages of the game will be used to conduct an exploratory factor analysis. Looking for common variations among the various game metrics may unearth underlying variables that better explain which EFs are associated with which game tasks. For each participant, their reaction times for the highest level they successfully complete will be used. Using regularized exploratory factor analysis owing to the small sample size, we can examine whether the conceptually different tasks do in fact target different EFs.

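### Exposed-versus-normative comparisons name no covariates, although exposure is not randomised and the main social and co-exposure variables are collected

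*Protocol article*

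**What the plan says.** All of this is in the protocol article.

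- **Baseline model (Data Analysis).** "the baseline NEPSY-II scaled scores of the intervention and control groups will be pooled and compared with the scores of the normative group", that is, 80 exposed children against 40 normative children. "This will also be done using a MANOVA with group membership as the predictor variable and the scaled scores of the 5 NEPSY-II domains" as outcomes.
- **Post-intervention three-group model (Data Analysis).** "Group membership will be the predictor variable, and domain scores will be the outcome variables".
- **Change scores (Data Analysis).** "These scores will be compared using a MANOVA with group membership as the predictor variable and changes in domain scores" as outcomes.
- **Covariates collected (Measures).** "In addition to alcohol use, data will be gathered on age, gravidity, parity, years of schooling, and household income". The Data Analysis section lists age with the other maternal variables, so it is taken here as maternal age.
- **Use of the covariates (Data Analysis).** Maternal data for the exposed groups are "pooled and compared with nonalcohol-exposed children to ascertain if there were significant differences between the 2 groups", by t tests with Bonferroni-adjusted values calculated as well. "Tobacco and drug use will also be compared among the alcohol-exposed and nonalcohol-exposed groups using a chi-square test". These analyses are labelled exploratory. No covariate is named in any NEPSY-II model, and nothing says what follows if the groups differ.
- **Normative group (Recruitment).** Its members are drawn with random number tables from children whose mothers' interviews show no exposure. No matching or stratification is described.
- **Hypotheses (Overview).** The second predicts lower baseline scores in exposed than in unexposed children. The third places the intervention group between control and normative after the intervention.

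**The concern.** Mothers who drank during pregnancy may differ from those who did not in schooling, income, parity, smoking and drug use, and these can be related to a child's test scores. If they do differ, a gap between 80 exposed and 40 unexposed children mixes those differences with any association with alcohol. The plan collects the variables needed to examine this but keeps them out of the outcome models.

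The planned significance tests do not fill the gap. With these group sizes a real imbalance can go unflagged and still shift the contrast, and a flagged one has no stated consequence.

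What is at stake is the reading of hypotheses 2 and 3. The Discussion expects the study to add to the literature on executive function after prenatal alcohol exposure whatever the trial result, and that contribution leans on the exposed-normative contrast. The normative benchmark for the intervention group after the intervention carries the same mixture.

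**Working it through.** **1. Which comparisons are exposed to confounding?**

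| Comparison | How the groups were formed | Confounding by maternal factors |
|---|---|---|
| Intervention v control (primary) | Block randomisation | None expected |
| Pooled exposed v normative, baseline | Observed exposure | Full |
| Intervention or control v normative, post-intervention | Observed exposure | Full |
| Change scores, three groups | Observed exposure for the normative contrast | Constant additive differences cancel; only differences in rate of change remain |

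The abstract and Study Procedures describe the normative group as formed by individual randomisation, and the Sample Size section speaks of randomising 120 children to three arms. For the normative group, the procedure under Recruitment is random selection from the unexposed. That makes the group representative of unexposed children in the pool. It does not balance exposed against unexposed.

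**2. Does the shared setting remove the problem?** Study Procedures notes that all children come from a low-SES environment. The Setting section reports marked income inequality in the area, and the Discussion expects to learn how the environments of exposed and unexposed children differ. Differences between mothers within the setting are therefore left open.

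**3. How large could it be?** The plan has no figure on this point to reproduce, and it gives neither an imbalance nor a covariate-score slope. Everything below is assumed, apart from the group sizes and the tests planned.

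Standard error of a standardised mean difference, 80 v 40: sqrt(1/80 + 1/40) = sqrt(0.0375) = 0.194 SD.

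Spurious gap = sum of (covariate imbalance × partial slope). With two covariates (schooling and income), each 0.5 SD apart:

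- slopes 0.15: 2 × 0.5 × 0.15 = 0.15 SD
- slopes 0.25: 2 × 0.5 × 0.25 = 0.25 SD

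Chance that a single score is significant at two-sided 0.05 with no alcohol effect, Φ(z − 1.96) + Φ(−z − 1.96), where z = gap / 0.194:

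| Spurious gap (SD) | z | P(significant) |
|---|---|---|
| 0.15 | 0.77 | 0.12 |
| 0.20 | 1.03 | 0.18 |
| 0.25 | 1.29 | 0.25 |

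A wider range, for one covariate 0.25 to 0.75 SD apart and correlated 0.2 to 0.4 with the score, gives gaps from 0.25 × 0.2 = 0.05 to 0.75 × 0.4 = 0.30 SD. The single-score rates are then 0.06 to 0.34.

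The planned test uses five outcomes jointly. Assume an inter-outcome correlation of 0.3 and the same gap on each outcome. The rejection rate is then 0.08 at 0.10 SD, 0.12 at 0.15, 0.18 at 0.20 and 0.38 at 0.30, close to the single-score rates.

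**4. Would the planned imbalance tests catch it?** Five maternal variables are tested by t test, so the Bonferroni level is 0.05 / 5 = 0.01 (critical value 2.58).

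| True imbalance (SD) | z | Flagged at 0.05 | Flagged at 0.01 |
|---|---|---|---|
| 0.4 | 0.4 / 0.194 = 2.07 | 0.54 | 0.30 |
| 0.5 | 0.5 / 0.194 = 2.58 | 0.73 | 0.50 |

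Both columns matter, because the Bonferroni values are calculated in addition to the ordinary ones. Even at 0.05, a 0.4 SD imbalance is missed nearly half the time.

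**The case against.** **The protocol makes no causal claim.** A reader might infer that the gap will be reported as an effect of alcohol. The text does not say so: hypothesis 2 predicts a group difference, and the Discussion itself expects environments to differ. The planned demographic comparisons would also let readers see measured imbalance. This stands. The most the document supports is that the gap may be read as an alcohol effect.

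**The normative group is a local benchmark.** Study Procedures and Measures give it the role of helping to interpret scores obtained with a US-normed test. For that purpose the unadjusted gap is a legitimate quantity. This also stands, and is why that estimate should be kept. It does not serve a hypothesis framed by exposure status.

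**The main question is untouched.** A reader might also infer that the trial's treatment comparison is confounded. It is not, because intervention and control are randomised.

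**Adjustment does not establish causation.** Unmeasured differences remain after any adjustment. That is true, and it calls for associational wording as well as adjustment.

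**A full analysis plan could hold the adjusted analysis.** This is a condensed article of a feasibility trial. But it states the predictor in each model and separately states what the covariates are for, so this is a stated choice and not only a detail left out.

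**Conclusion.** The point holds for the baseline exposed-normative MANOVA and the post-intervention contrasts with the normative group. These are observational comparisons with group as the sole named predictor, while the maternal and co-exposure variables serve only exploratory tests. The primary comparison is unaffected, and the change-score comparison is affected much less.

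The size cannot be established from the documents. If confounding produced a gap of 0.15 to 0.25 SD and alcohol had no effect, a single score would be significant about 12% to 25% of the time instead of 5%. That rests on assumed imbalances and slopes and on normal approximations. It shows what could happen and does not predict what this sample will show. The improvement is worthwhile and cheap; the point does not threaten the trial's main conclusion.

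**What to change.** 1. Keep the unadjusted exposed-normative gap and label it the local benchmark.
2. Beside it, report a MANCOVA or regression for the baseline and post-intervention normative contrasts, with a covariate set stated before analysis: maternal schooling, household income, maternal age, parity, tobacco use and drug use. Do not choose covariates by significance test.
3. Treat child age as optional, since NEPSY-II scaled scores are already age-normed.
4. Word both the unadjusted and the adjusted result as associations with exposure.
5. Leave the randomised intervention-control comparison outside this change.

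No new data are needed, because the plan already obtains these variables at recruitment. The cost is a little more analysis and about six degrees of freedom if each covariate takes one: from 120 − 2 = 118 for the pooled contrast, and from 40 + 40 − 2 = 78 for intervention versus normative.

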### Study Procedures

Alcohol-exposed children, as assessed by maternal interviews, will be randomized into an intervention or a control group with 40 participants in each group, using block randomization. The maternal interview will contain questions regarding alcohol use just before and during pregnancy, including the number of standard units of alcohol consumed, with 3 standard units being the threshold for determining alcohol exposure. A group of 40 unexposed children will be randomized in a group to provide normative data using individual randomization. An overview of the study design is shown in Figure 1. As the participants are drawn from a low-SES and resource-poor environment, the performance of the normative group will serve as a more suitable gauge of cognitive development in the participants’ specific contexts. This will enable us to better interpret the results of the neurodevelopmental assessments.

The SPIRIT schematic is shown in Table 1. Baseline assessments examining cognitive function will be conducted with all 3 groups. The intervention group will then play the FARR game twice a week for 6 months (40 play sessions in total). Post intervention, all 3 groups will receive follow-up cognitive assessments. Data gathered by the game will also be collected from the intervention group. All participants will start the intervention at the same level of difficulty. They will be given the opportunity to play the game during hour-long sessions facilitated by community workers. Play will, however, be self-directed; participants will be encouraged to play but will be allowed to stop at any time during a session. As participants log into the devices, they will be able to continue at the difficulty level they had previously reached.

There are 4 different stages in the game of increased complexity. After 10 trials in a stage, a participant automatically moves on to the next for 10 trials. After the fourth stage, participants start at the first stage again. The difficulty of each stage varies independently based on a participant’s performance. Getting 8 or more correct increases difficulty, getting fewer than 4 correct decreases difficulty, and otherwise the difficulty remains the same.

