#### Sample Size

A total of 120 participants will be recruited and randomized to one of 3 study arms. This is in line with the sample sizes of previous studies looking at FASD and cognitive functioning [9,19,39]. Previous studies of this nature showed a medium effect size [42-45]; however, owing to the differences in method and there not being interventionists involved in the training sample, size calculations were done for a small (*d*=0.2) effect size. With a significance level of .05, 120 participants in 3 groups would yield a statistical power of 0.79 for the repeated measures multivariate analysis of variance (MANOVA) comparing the performance between the 3 groups.

There are approximately 46 ECD centers, and in SBM area, 1593 children aged between 3 and 5 years have enrolled at these centers and 1635 6-year-olds have enrolled in Grade R [46]. Assuming a prevalence rate of 24% of consuming alcohol during pregnancy on the basis of a prevalence study conducted in SBM area [31], it should be possible to reach the desired sample size through 400 interviews.

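### The ordering and greater-improvement hypotheses are given only omnibus comparisons across the groups beyond the primary test, with no stated contrast that could establish either claim

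*Protocol article*

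**What the plan says.** The Overview lists the hypotheses. Two are at issue. One is an ordering after the intervention: control lowest, intervention in the middle, normative highest. The other concerns change: "the intervention group will show greater improvement on psychometric assessments of EFs than the control and normative groups". The same list predicts that exposed children will already score below unexposed children at baseline.

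Data Analysis assigns the tests as follows.

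- **Primary hypothesis:** a two-group MANOVA of intervention against control on post-intervention scores, with five scores as outcomes.
- **Ordering:** "Postintervention NEPSY-II scaled scores (see Table 1) of the intervention, control, and normative groups will be compared using a MANOVA".
- **Greater improvement:** difference scores are calculated for every participant, and "These scores will be compared using a MANOVA with group membership as the predictor variable and changes in domain scores". Three groups are implied here, not named.

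Each MANOVA is followed by discriminant analysis. No contrast, pairwise comparison or direction is stated for the ordering or the improvement hypothesis.

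On how the groups arise, Study Procedures has exposed children "randomized into an intervention or a control group with 40 participants in each group", and separately: "A group of 40 unexposed children will be randomized in a group to provide normative data using individual randomization". The normative children are therefore a random selection from unexposed children. They are not randomised against the exposed ones.

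**The concern.** Both hypotheses are statements about named pairs of groups with a named sign. An omnibus MANOVA asks only whether any of the group mean vectors differ. It would reject just as readily if controls did better than the intervention group. Discriminant analysis describes how the groups separate, but it does not test a chosen pair.

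The normative group is expected to differ from the exposed groups whatever the game does, because the protocol predicts this itself. The three-group test on post scores therefore mixes a randomised comparison with an observational one, and the observational part alone can make it significant. If such a result were reported under the ordering hypothesis, it could be taken as support for the game when it reflects only prenatal exposure. For improvement, the randomised comparison of change between intervention and control appears nowhere in the plan.

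**Working it through.** **1. The plan's own figure.** Sample Size states: "With a significance level of .05, 120 participants in 3 groups would yield a statistical power of 0.79", for a "repeated measures multivariate analysis of variance (MANOVA) comparing the performance between the 3 groups"; "size calculations were done for a small (*d*=0.2) effect size". For a repeated-measures design with 3 groups, m = 2 visits and N = 120 (df 2 and 117), the group-by-time noncentrality is λ = f²·N·m/(1 − r).

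- Entering 0.2 as f with r = 0: 0.04 × 120 × 2 / 1 = 9.6, power 0.788.
- Entering f = 0.1 (d = 0.2) with r = 0.75: 0.01 × 120 × 2 / 0.25 = 9.6, power 0.788.

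So 0.79 can be reproduced, but only with inputs the article does not state. The figure describes the omnibus test and says nothing about power for either pairwise claim. It is not needed for what follows.

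**2. Hypotheses against stated tests.**

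| Component | Stated test |
|---|---|
| Post score, intervention above control | Primary two-group MANOVA (non-directional) |
| Post score, intervention below normative | None; three-group omnibus only |
| Change, intervention above control | None; omnibus only |
| Change, intervention above normative | None; omnibus only |

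**3. What the omnibus tests do when the game has no effect.** From the documents: 40 children per group, 5 outcomes, α = 0.05. Assumed, because the documents give no values: unit-variance outcomes with pairwise correlation ρ = 0.3 or 0.5, pre-post correlation 0.6, and the same exposed-normative gap δ on all five outcomes.

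Wilks' Λ has an exact F in both cases:
- three groups: F = [(1 − √Λ)/√Λ]·(N − p − 2)/p, df 2p and 2(N − p − 2), here 10 and 226;
- two groups: F = [(1 − Λ)/Λ]·(n − p − 1)/p, df p and n − p − 1, here 5 and 74.

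The size of the gap enters through D² = δ²·p/[1 + (p − 1)ρ], multiplied by 40 × 80/120 = 26.7. At δ = 0.5 this gives 0.25 × 5/2.2 × 26.7 = 15.2 for ρ = 0.3, and 0.25 × 5/3 × 26.7 = 11.1 for ρ = 0.5. Rejection is therefore lower at the higher correlation.

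Rejection rates with zero intervention effect (4,000 runs per scenario, ρ = 0.3 / 0.5):

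| Gap, same at both visits | Three-group, post scores | Three-group, change scores |
|---|---|---|
| 0 | 0.05 / 0.05 | 0.05 / 0.05 |
| 0.2 SD | 0.14 / 0.11 | 0.05 / 0.05 |
| 0.3 SD | 0.28 / 0.20 | 0.05 / 0.05 |
| 0.5 SD | 0.72 / 0.58 | 0.05 / 0.05 |
| 0.8 SD | 1.00 / 0.97 | 0.05 / 0.05 |

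A separate run with Pillai's trace (3,000 runs) gave 0.27 / 0.20 at 0.3 SD and 0.72 / 0.55 at 0.5 SD. The ranges 20-28% and 55-72% span both runs. The intervention-control comparison stays at 0.042-0.057 in every scenario, on post and on change scores.

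**4. When the gap moves.** Starting from 0.5 SD, a shift of 0.2 SD over the six months makes the change-score omnibus reject in 0.16 / 0.12 of trials, and a shift of 0.3 SD in 0.34 / 0.25, still with no intervention effect.

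**5. The post-score omnibus does not track the intervention effect.** With ρ = 0.3 and a 0.5 SD gap, it rejects in 72% of trials when the effect is zero and in 58% when the effect is 0.2 SD, because a partly effective game moves the intervention group towards the normative one. At an effect of 0.5 SD the intervention and normative means coincide, so the ordering hypothesis is false, yet the test rejects in 75%.

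**The case against.** Four points can be made for the plan.

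- **The primary test already compares intervention with control.** This is right. A reader might infer that the ordering hypothesis rests solely on the omnibus. It does not, because the two-group MANOVA covers its intervention-control half on post scores, and the normative gap does not disturb that test.
- **The rejection rates are not false-positive rates.** Also right. If unexposed children truly differ, the three-group null is false and rejecting it is correct. A reader might take 55-72% as type I error inflation of the planned test; it is not. The rates show only that a significant omnibus is no evidence for the game. The article does not say it would be read that way, and it introduces the later comparisons as further analysis.
- **A gap between groups cancels in difference scores.** True for a stable gap, so the exposure gap as such cannot be said to drive the improvement test. Only a changing gap can. The Discussion expects the study to show how development differs in exposed children, so parallel trajectories cannot be taken for granted, but nothing in the documents shows that the gap will move.
- **A condensed article may leave follow-up contrasts to the analysis plan, and discriminant centroids do show the order of the groups.** This carries some weight. However, the article does more than stay silent: it names the procedure for each comparison, and those procedures cannot establish the hypotheses. Centroids describe an order without testing it.

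**Conclusion.** The point holds in limited form. The named analyses do not answer two of the protocol's own hypotheses. Three of the four pairwise components have no stated test, including the randomised comparison of change. The three-group post-score MANOVA can be significant from the exposed-normative gap alone: about 20-28% of the time at 0.3 SD and 55-72% at 0.5 SD. The change-score MANOVA holds at 5% under a stable gap and rises to about 12-16% if the gap shifts by 0.2 SD.

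These sizes rest on assumed gaps, a gap equal across all five outcomes, outcome correlations of 0.3-0.5 and, for change scores, a pre-post correlation of 0.6. That an omnibus test cannot establish the order or the direction depends on none of them. The primary intervention-control comparison on post scores is unaffected.

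**What to change.** Pre-state the following contrasts, each with a confidence interval, on the five scores (or on a summary of them fixed beforehand), under one multiplicity rule.

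- **Ordering:** intervention minus control, and intervention minus normative, both on post scores. Leave the normative contrast unadjusted for baseline and label it observational. Baseline adjustment would change the question: with an assumed stable gap of 0.5 SD and a pre-post slope of 0.6, the contrast shrinks from −0.5 to −0.5 + 0.6 × 0.5 = −0.2 SD.
- **Improvement:** intervention minus control on change scores or, preferably, on baseline-adjusted scores, as the randomised comparison; and intervention minus normative on change scores, labelled observational.
- **Decision rule:** claim ordering, or greater improvement, only if both relevant contrasts have the hypothesised sign and their intervals exclude zero. Base any claim of an intervention effect on the intervention-control contrast alone.
- **Descriptive only:** the three-group MANOVAs and the discriminant analyses.

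The cost is analysis wording, a few extra contrasts and a small multiplicity penalty. No new data are needed. The change makes the claims interpretable but does not add power: with an effect of 0.2 SD on every score (ρ = 0.3), the two-group MANOVA rejected in 14% of simulated trials on post scores and 17% on change scores.

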### Eligibility Criteria

#### Inclusion Criteria

Children aged between 4 and 6 years will be eligible for inclusion. Children must reside in the SBM area and attend or be enrolled in an ECD center.

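### The game-performance correlation pairs a raw count of game levels with age-normed NEPSY-II scores and makes no allowance for the child's age, which may dilute it

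*Protocol article*

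**What the plan says.** The Data Analysis section of the protocol article defines improvement in the game, stage by stage, as "quantified as how many difficulty levels a participant has successfully completed". It then names the statistic: "This will then be correlated with performance in the NEPSY-II domain scores in a covariance matrix using the Pearson correlation coefficient". The correlation sentence does not itself say which type of NEPSY-II score is meant, but the primary analysis in the same section uses "the scaled scores of the 5 NEPSY-II domains".

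The two variables treat age differently:

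- **NEPSY-II.** The Measures section states: "Scores obtained on the subtests of the NEPSY-II are compared with the scores of a normative group based on age".
- **Game.** Under Study Procedures, "All participants will start the intervention at the same level of difficulty". A child moves up a level after 8 or more correct answers in 10 trials and down after fewer than 4. These are absolute thresholds, the same at every age.

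The age range is set under Inclusion Criteria: "Children aged between 4 and 6 years will be eligible for inclusion". Only the intervention group, planned at 40 children, produces game data. No age covariate, partial correlation, age stratum or age-standardised game score is named for this analysis. The separate analysis of 6-year-olds serves the additional subtests and does not adjust the main correlation. The demographic comparisons compare exposed with unexposed groups and do not bear on it either.

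**The concern.** Norming removes age from one side of the correlation and leaves it in the other. Take a younger and an older child, each exactly average for age. Their scaled scores are equal, but their level counts differ if older children climb further. Such pairs widen the spread of the game score without adding to its covariance with the NEPSY-II score, so the Pearson coefficient is pulled toward zero even when the link within any one age is real.

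That older children reach higher levels is an inference, but the protocol makes it plausible. The test is scored by age, some subtests are reserved for 6-year-olds, and the pilot had to check that stimulus timing suited the children's age.

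At stake is the secondary hypothesis that improvement in the game goes with improvement in executive function. With about 40 children, a moderate loss of correlation can turn a detectable link into a non-significant one.

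**Working it through.** **Nothing to reproduce.** The protocol states no expected correlation, power or sample size for this analysis. Its power figure of 0.79 belongs to the MANOVA.

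**Inputs from the protocol.** n = 40 (intervention group, no losses assumed); significance level 0.05, taken as two-sided.

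**Assumed inputs, not in the protocol.** The within-age correlation r; the correlation a of age with levels completed (r_age); the correlation c of age with the scaled score.

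**Formula.** The unadjusted correlation is

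r_obs = r x sqrt((1 - a^2)(1 - c^2)) + a x c.

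If the norms fully remove age (c = 0), this reduces to r_obs = r x sqrt(1 - a^2).

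**Coefficient with c = 0 and r = 0.40**

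- a = 0.3: 0.40 x sqrt(0.91) = 0.382
- a = 0.5: 0.40 x sqrt(0.75) = 0.346
- a = 0.7: 0.40 x sqrt(0.51) = 0.286

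**Power by Fisher z.** Unadjusted power is approximately Phi(atanh(r_obs) x sqrt(n - 3) - 1.96). For a = 0.5: atanh(0.346) x sqrt(37) = 2.20, and Phi(0.24) = 0.59. The partial correlation gives up one degree of freedom: atanh(0.40) x sqrt(36) = 2.54, and Phi(0.58) = 0.72.

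| Assumed r | Age-adjusted power | Unadjusted, a = 0.3 | Unadjusted, a = 0.5 | Unadjusted, a = 0.7 |
|---|---|---|---|---|
| 0.30 | 0.46 | 0.43 | 0.37 | 0.26 |
| 0.40 | 0.72 | 0.69 | 0.59 | 0.43 |
| 0.50 | 0.91 | 0.88 | 0.81 | 0.62 |

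Simulation with 20,000 trials at r = 0.40 agrees within about 0.02: 0.73 age-adjusted, against 0.70, 0.59 and 0.44 unadjusted.

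**Price of adjusting when age does not matter.** At a = 0 and r = 0.40, the unadjusted power is 0.73 and the adjusted power 0.72.

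**If the norms leave an age trend (hypothetical).** With r = 0.40 and a = 0.5, c = -0.2 gives 0.40 x sqrt(0.75 x 0.96) - 0.10 = 0.24, and c = +0.2 gives 0.44. The bias can therefore go either way.

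**The case against.** **The size is unknown.** The protocol gives neither the age-to-levels correlation nor the within-age correlation. At a = 0.3 the loss, 0.40 to 0.38, is negligible. Play is self-directed and a child may stop at any time, so levels also reflect engagement, which could leave age a small share. This stands.

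**The statistical analysis plan may add age.** It is not shown, and a partial correlation is still of Pearson type. That is possible. But the protocol fixes both the game metric and the coefficient and names no age term, so the choice as written can be improved.

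**The error is conservative.** If the norms work here, the unadjusted coefficient understates a link and does not create one. This stands.

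**It overlaps with prior ability.** A common starting level lets any initial advantage show up in the count, and age is one such advantage. Partly stands: age adjustment removes only the age component.

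A reader might infer more than the text supports in three ways:

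- *That age will manufacture a correlation.* With no within-age link, c of 0.2 to 0.3 in either direction would raise a 5% test to about 9% to 15% rejections at a = 0.5, and 14% to 25% at a = 0.7. These figures need an age drift in the scaled scores that the protocol does not state. The Measures section says the norms come from a US sample and that "This group will differ significantly from the populations of interest in this study", but it goes on to call the test relatively insensitive to language and culture. A uniform shift would leave the coefficient unchanged.
- *That a screening-tool decision rests on this coefficient.* The Discussion says only that, after strong correlations, further studies could examine that use.
- *That two children average for their ages count against a link.* They add variance to the game score and almost nothing to the covariance. That is dilution, not contrary evidence.

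**Conclusion.** The point holds as a mismatch in the stated analysis: a level count with no age norming is correlated, unadjusted, with an age-normed score across ages 4 to 6. The expected consequence is dilution by sqrt(1 - r_age^2). This assumes that older children reach higher levels and that the norms remove age from the NEPSY-II score in this sample. With an assumed within-age correlation of 0.40 and 40 children, the loss is trivial at r_age of 0.3 or less and material from about 0.5, where power is 0.59 instead of about 0.73. Distortion in either direction is a possibility only if the US norms leave an age trend here. The matter concerns a secondary hypothesis analysed within one arm and leaves the randomised comparison unaffected. It is worth correcting because the correction is nearly free, not because a large error has been shown.

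**What to change.** In the Data Analysis section, make the game-performance analysis a partial correlation, or equivalently a linear regression, adjusted for the child's age in months at baseline, for each pairing of game stage with NEPSY-II score. Report the unadjusted Pearson coefficient beside it, so that readers can see how much age contributes.

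The cost is one line of wording and one degree of freedom. Age is already needed for eligibility and for NEPSY-II scoring, so no new data are required.
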